### Engagement With Participants With Lived Experience of IPV

#### Overview

Women who have experienced IPV have an increased risk of adverse outcomes when participating in research [43]. The NHMRC recognize people who have experienced social and economic disadvantage, such as trauma and violence, may have potential limitations with their decision-making ability [43]. To mitigate and minimize these risks, consultation with end users, such as social workers from Women’s Safety Services SA, will occur prior to the interviews with phase 1 participants to ensure the questions, activities, and discussion is a trauma-informed and healing approach [40]. To ensure victim-survivors are central to the design and empowered by the process, the research will align with best practice principles for coproduced research with victim-survivors and use a framework developed by Lamb et al [40] to support ethical coproduction of research with vulnerable populations of women. These best practice principles align with the NHMRC principles of justice, respect, and beneficence [43].

#### Distress Protocol

A distress protocol has been developed to ensure the research team is able to respond to participant distress. The flowchart was developed in alignment with recommendations from Whitney and Evered [45], Draucker et al [46], and Labott et al [47] and includes resources and support services (refer to Multimedia Appendix 2). The development of the distress protocol was in collaboration with the advisory group and supervisory team. At the completion of engagement, all participants of each phase will receive a pamphlet with detailed immediate and ongoing psychological support services that are available to access in person and/or online (refer to Multimedia Appendix 3).

#### Advisory Group

An advisory group, formed through connections with potential end users, will provide guidance throughout the research with an aim to reduce the risk of causing harm for those with lived experience. Six monthly meetings are planned to discuss the proposed research methodologies and intervention. The purpose is to ensure the program supports the needs of women with lived experience in addition to promoting a safe space that protects the well-being of those with lived experience and health professionals throughout the research.

#### Confidentiality

During data collection, analysis, and reporting, the participants will be labeled using predefined codes (Midwife 1, Social Worker 1, and Woman 1). This process is known as the dominant approach to addressing confidentiality and will be applied during the 3 phases of the process: data collection, data cleaning, and dissemination [48]. The women with lived experience will be informed that generalized, descriptive characteristics will be collected, and information will not be identifiable in the reporting process. This is similar to the health professionals whereby their generalized characteristics, for example, occupation and experience will be included, but not identifiable to maintain confidentiality and anonymity [48]. Identifying information will be stored separately from the transcripts. A deidentified dataset will be analyzed and disseminated, aiming to protect the confidentiality and anonymity of participants [48]. The PIS form provided to focus group participants will have a statement that while confidentiality will be maintained from the researcher’s perspective, participants are also obligated to maintain confidentiality across the focus group discussions given the public nature of the forum.

#### Vicarious Trauma

Due to the nature of the research, there is potential for the researchers involved to experience vicarious trauma. Vicarious trauma can occur from burnout, traumatic stress, and compassion fatigue [49]. The research team will have access to the Employee Assistance Program in preparation for potential discomfort or in response to trauma experienced. All research members will be asked to reflect on their involvement and are aware of the potential challenges of working in this field and agree to embrace differences in perspectives. The supervisory team will have the flexibility to opt into the phases of the research to ensure their comfort, and feedback will be sought iteratively throughout the project to ensure nonmaleficence.

### Procedure

#### Phase 1: Exploration

##### Overview

The objective of the interviews with women with lived experience of IPV is to understand their perspectives of engaging with maternity care services in South Australia (research question 3). The themes emerging from the interviews will offer valuable insight and inform the development of the workshop, ensuring it reflects and addresses the needs of women with lived experience in South Australia. From there, the importance is shifted to exploring the current interprofessional education and training on IPV received by maternity care providers in South Australia, to then examine their perceptions of its relevance and effectiveness (addressing research question 2). The focus groups aim to cultivate an understanding of each discipline’s roles, responsibilities, and values in relation to collaboration with other disciplines when navigating care for women with lived experience or IPV in pregnancy.

##### Lived Experience Interviews

Semistructured interviews will be used to explore the experiences and perceptions of maternity care among women with lived experience of IPV. The semistructured interviews allow for deeper exploration and the provision of participant autonomy to deviate and explore emerging concepts that may arise throughout the interview and further enhance the understanding of the issues [34,50]. The interview guide will be developed following the data extraction of the scoping review and reviewed by an advisory group and the supervisory team.

##### Data Saturation: Interviews

It is expected that data saturation will occur after a minimum of 9‐10 interviews [51]. Braun and Clarke [52], however, suggest researchers avoid limiting data collection to a specific number, and therefore in this study, the continuation of interviews will occur until data richness is achieved, and there is notable repetition in the presenting themes and codes.

##### Health Professional Focus Groups

Focus groups are incorporated due to the known benefits of exploring a group of health professionals’ opinions, perspectives, and views to ensure the richness of data [53]. Focus groups are particularly important when exploring new insights and understanding poorly explored topics as communication can be enhanced through a process defined as sharing and comparing [54]. The questions and activities will be structured and planned, commencing with an introduction, transition, and key questions followed by a final activity or question [55]. A range of group activities will be conducted, such as asking the group to arrange a series of statements in a particular order acknowledging that a consensus may not always be reached. The purpose is to observe the insights that arise [56]. The focus groups will be facilitated by 2 members of the research team to reduce bias [55].

##### Data Saturation: Focus Groups

A total of 4‐8 focus groups is recommended to achieve data saturation, with approximately 4‐8 participants in each group [51,54].

##### Data Analysis

Data will be analyzed by the primary investigator following the 6 steps to reflexive thematic analysis by Braun and Clarke [52] to determine the patterns and themes from the data. These iterative steps will ensure the data is interpreted and represented meaningfully [52]. The qualitative data will be collected in phase 1 and recorded and transcribed verbatim (by the principal researcher for the victim-survivor interviews and potentially an external third party for the focus groups) for the purpose of identifying, analyzing, and acknowledging patterns that come from the data [52,57]. Analysis will begin with familiarization of the data through transcription and rereading the transcripts to develop a deeper understanding [52,58]. Initial codes will be generated from identified patterns in the data [52]. Reflexive thematic analysis does not require a team of researchers to review codes; instead, the coding process is an “organic” process and does not adhere to specific frameworks [59]. One team member will independently code all data and share the findings with the research team. To improve trustworthiness and confirmability of the data, small portions of the transcripts will be allocated to differing authors, to confer, reflect, provide feedback, and therefore ensure a consensus is reached [60]. Trustworthiness in qualitative research can be strengthened further through reflexive processes [60]. Credibility in this study will be maintained through reflexive journaling to acknowledge personal biases to maintain an objective stance in the collection and data analysis processes [60].

After coding, the initial codes are reevaluated due to the reflexive, iterative nature of the 6 steps described by Braun and Clarke [52] and overarching themes of the data will be sought and determined. The continual reflection and review of the codes and themes will ensure the data represents the whole picture [52]. Once refined, the themes are then clearly defined and titled to articulate the meaning of the data [52]. Finally, the analysis is reported in a manuscript to present to the wider community [52].

The reflexive thematic analysis of focus groups with health care professionals and the interviews with victim-survivors will occur separately. While both qualitative data collection occurs in the same phase, each has a differing purpose and thus the research and analysis will be undertaken and reported separately.

### Phase 2: Development of the Advancing Learning in Gender-Based Violence Through Interprofessional Networks Workshop

The simulation-based workshop, referred to as “Advancing Learning in Gender-Based Violence through Interprofessional Networks” (ALIGN), will be developed following the phase 1 qualitative findings, as part of phase 2 of the broader project. The proposed structure of the day will incorporate 4 IPV scenarios, each with a differing focus. The structure will follow best practice standards, outlined by The International Nursing Association for Clinical Simulation and Learning Standards Committee, through the incorporation of structured learner activities, including a prebrief, simulation, and debrief format to ensure transferability and consistency of the program [61].

Simulation education through role play and facilitated discussions is known to improve the participants' knowledge in the clinical environment [58,62]. The proposed simulation-based education program will follow recommendations from the World Health Organization (WHO) through the development of learning objectives that are in alignment with their key recommendations for IPV-focused education for health professionals (clinical skills, resources, behaviors, and values) [58,63]. However, as the program aims to also influence health care professionals’ collaboration, the overall program objectives will be combined with the interprofessional competencies as defined by IPEC: values and ethics, roles and responsibilities, communication, teams, and teamwork [64]. This will support the effective delivery of the simulation workshops intended objectives, which are as follows:

Apply their own professional role and responsibilities in the clinical scenario, as well as describe the professional role and responsibility of other health professionals when responding to IPV.To improve generalized knowledge of violence against women in the perinatal context and recognizing it as a significant public health concern.Demonstrate ethical and women-centered care when responding, while acknowledging their own personal values and biases to actively collaborate with the interprofessional team.Communicate in a trauma-informed, respectful manner with victim-survivors and interprofessional team members, sharing relevant information and providing feedback to support coordinated, safe, and supportive care.

### Phase 3: Evaluation

#### Overview

The evaluation of the ALIGN workshop will involve a single-group quasi-experimental pretest-posttest design (phase 3). The aim of phase 3 is to evaluate the perceived impact of the simulation-based interprofessional education intervention on health care professionals’ collaboration, knowledge, and behavioral responses to IPV disclosures during the perinatal period, addressing research question 4.

#### Data Collection Tools

A pre- and postquestionnaire will be used to assess the knowledge, attitude, and practice changes of participants. The preworkshop questionnaire will establish a baseline; the postworkshop questionnaire will therefore measure immediate effects on participant knowledge, attitude, practice, and behavior [65]. There will be another follow-up questionnaire at the 4-month postintervention, that is designed to capture practice changes [66].

The questionnaire will be structured to evaluate the Knowledge (multiple choice and binary questions [true or false and yes or no]), Attitudes (Likert scale), and Practices (simulated video scenarios with rubric), referred to as the Knowledge, Attitudes, and Practices (KAP) framework. The KAP framework allows for the exploration of a population to assess knowledge (what is known), attitudes (what is believed), and practices (what is done) [65,67]. Additionally, these questions may identify knowledge gaps and behavioral patterns, aligning with the program’s goal of assessing the impact and informing future improvements [67]. The knowledge-based questions will be formulated at the conclusion of the phase 1 qualitative data collection.

To evaluate a change in collaborative practices, the evaluation of the program will integrate the validated 16-question IPEC competency self-assessment tool into the questionnaire [22,68]. This instrument provides a validated means of assessing interprofessional competencies by measuring the participants’ self-efficacy, in relation to the IPEC core competency framework [68]. The IPEC competency self-assessment tool is reliable and validated and can therefore be used to assess the development of the participants’ collaborative practice skills [68].

Changes in interprofessional practice will also be objectively assessed using predefined scoring rubrics, with standardized criteria applied to minimize interrater variability. This process will involve participants watching a simulated video, aligned with the program’s learning outcomes. The participants will be asked to provide a written response that will be graded using a standardized rubric before and after the intervention.

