### Objectives

The objectives of the study are as follows:

To design and develop a simulation workshop for health professionals that captures the experiences of women with lived experience of IPV in pregnancy in addition to addressing the needs of health professionals providing that care.To evaluate the perceived impact of the simulation workshop to determine the changes in the health professional’s collaboration and behavioral response to IPV disclosures and ongoing management of care throughout the perinatal context.To evaluate changes in participants’ objective knowledge related to recognizing and responding to IPV disclosures during maternity care following a simulation-based interprofessional education intervention, using standardized pre- and postintervention knowledge measures.To evaluate changes in participants’ interprofessional responses to simulated IPV disclosure scenarios, using standardized assessment that is scored with predefined rubrics before and after the intervention.

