#### Content Validity

The construction and validation of the knowledge, attitudes, and practice aspect of the questionnaire will be developed in alignment with the instrument development model [69]. The IPEC questions are validated and therefore do not require further validation.

Content validity will be achieved through review of the questionnaire by experts across varying health professionals from the targeted 5 discipline groups [70]. This is not a statistical test; yet, it aims to ensure the questionnaire explores the contextual issues [70]. This process will remain iterative, and the questionnaires will be adapted until each expert agrees on the final set of questions.

The scoring rubrics for the assessed scenarios in the pre- and postquestionnaire, will be developed in alignment with the WHO curriculum guidelines for training health care providers in responding to IPV [63]. Interrater consistency will be supported through assessor collaboration and the use of standardized scoring criteria. Interrater reliability will be measured through the kappa statistic to ensure that the data collected correctly measure the variable prior to the implementation of the project [71]. There will be 2 independent assessors who will grade all data requiring scoring through the rubrics. This process will be refined by piloting the rubric before implementation.

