The IPEC tool and attitudes and practice Likert scale responses will be summed to generate a total score and domain-specific scores; higher scores indicate greater self-reported competency. The participant self-reported changes for each domain, and overall scores will be evaluated using a 2-tailed, paired *t* test to determine the mean and SD over time [78]. The Wilcoxon signed-rank test, however, will compare individual ordinal data for each Likert question to compare and determine the statistical significance.

The assessment of the video scenario questions will be scored in ordinal domains based on the rubrics and compared pre- and postinterventions using the Wilcoxon signed-rank test. The total rubric score will be analyzed through a paired *t* test.

Multiple comparisons arise from testing more than one outcome through different methods. Given the exploratory nature of the project, there will be no formal adjustment to multiple comparisons applied; instead, the results will be interpreted cautiously with consideration of the effect sizes and CIs. All data will be displayed in tables.

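### The rubric outcome behind objective 4 has no stated protection against leniency that both assessors share toward post-workshop answers, and kappa cannot detect such leniency

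*Protocol article*

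**What the plan says.** The fourth objective in the Protocol article (Objectives) is to evaluate change in responses to simulated disclosures, "using standardized assessment that is scored with predefined rubrics before and after the intervention". Under Phase 3, Data Collection Tools, participants watch a simulated video and write an answer: "The participants will be asked to provide a written response that will be graded using a standardized rubric before and after the intervention". The same section gives the outcome its status: "Changes in interprofessional practice will also be objectively assessed using predefined scoring rubrics, with standardized criteria applied to minimize interrater variability".

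The scoring safeguards are under Content Validity. The rubric follows WHO training guidance and is piloted, assessors collaborate to keep scoring consistent, and "There will be 2 independent assessors who will grade all data requiring scoring through the rubrics". On agreement the section says: "Interrater reliability will be measured through the kappa statistic to ensure that the data collected correctly measure the variable". That check is placed before the project is implemented.

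Under Data Analysis, the answers are "scored in ordinal domains based on the rubrics" and compared before and after by the Wilcoxon signed-rank test. The total rubric score goes to a paired *t* test. The Phase 3 Overview describes a single-group pretest-posttest evaluation, and Sample Size sets a minimum of 42 participants.

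**The concern.** With one group and no control, whatever makes assessors score later answers more generously enters the estimated change in full and cannot be separated from the effect of the workshop. Assessors who can tell a post-workshop answer from a pre-workshop one may expect it to be better. Two assessors working from one rubric reduce individual error, but they do not remove an expectation that both hold. If the answers were graded in two successive rounds, a gradual change in strictness would also coincide with time.

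The stated purpose of kappa adds to the problem. Kappa shows how far two assessors agree beyond chance. It does not show that the scores are correct, and two equally lenient assessors can agree very well.

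At stake is the one practice outcome that does not depend on participants rating themselves: the IPEC tool and the Likert items are self-report. A biased rubric score would be read as independent confirmation of those self-reports.

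**Working it through.** **1. Safeguards against threats.** The sections on data collection, validity, analysis and confidentiality were read for anything that hides the time point or mixes the scoring order.

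| Stated safeguard | Disagreement between assessors | Leniency shared by both toward post answers |
|---|---|---|
| Predefined rubric, standardized criteria | yes | narrows discretion, does not remove it |
| Two independent assessors | yes | no |
| Assessor collaboration | yes | no |
| Piloting the rubric | yes | no |
| Kappa before implementation | yes | no |
| Coded labels and deidentified data (Confidentiality) | not relevant | no: codes of the form profession plus number show discipline and do not hide time point |

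No section masks the time point, pools the answers or randomizes the grading order.

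**2. Size of the effect on the paired *t* test (illustration).**

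Inputs: n = 42 (Sample Size). Two-sided alpha 0.05 is assumed; two-tailed testing is stated for the self-report scores and taken to apply to the rubric total. The true change is set to zero. The bias b, in SDs of the paired difference, is assumed, because the article gives no basis for a value.

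The test statistic follows a noncentral *t* distribution with 41 degrees of freedom and noncentrality b × √n, where √42 = 6.481. The critical value is 2.020. The probability of P<.05 is P(T > 2.020) + P(T < −2.020).

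| b | b × 6.481 | Probability of P<.05 |
|---|---|---|
| 0 | 0 | 0.050 |
| 0.1 | 0.648 | 0.097 |
| 0.2 | 1.296 | 0.244 |
| 0.3 | 1.944 | 0.476 |

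For scale, the smallest true change that this test detects with 80% power at n = 42 is 0.44 SD (0.4428 × 6.481 = 2.869 gives 0.80). A bias of 0.2 SD would be nearly half of that.

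**3. Would kappa reveal it?** Two assessors were simulated on one four-level domain. All settings are assumed: cut points at −0.8, 0 and 0.8 on a standard normal latent score, pre-post correlation 0.6, independent assessor error with SD 0.35, and the mean of the two scores analysed. A leniency shared by both assessors was added to post answers only.

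| Shared leniency (latent SD) | Kappa on post answers, unweighted | Kappa on post answers, quadratic-weighted | Spurious standardized change | Probability of P<.05, n = 42 |
|---|---|---|---|---|
| 0 | 0.52 | 0.82 | 0.00 | 5% |
| 0.2 | 0.52 | 0.82 | 0.19 | 23% |
| 0.3 | 0.52 | 0.82 | 0.28 | 43% |
| 0.5 | 0.53 | 0.82 | 0.47 | 84% |

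Kappa hardly moves while the false-positive rate rises steeply. This holds for either weighting, and it would hold for kappa computed on study answers as well as on pilot answers.

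**The case against.** The strongest reply is that the article is silent on masking and does not say that assessors are unmasked. Grading before and after identifies which answers are graded; it does not say that grading takes place in two labelled rounds. A reader might infer that assessors will know the time point. The documents do not support that; they support only that nothing stated prevents it. Label removal and batch order could also sit in a fuller protocol. That reply has force, but the article does list its scoring safeguards and calls the outcome objective on their strength, and those safeguards miss this threat.

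A reader might also trace the bias to agreement being checked before implementation only. That does not follow: the simulation shows that kappa on study answers would miss it too. Nor is there ground for saying that an unsuitable kappa was chosen. Its weighting is not stated, and no section applies it to the total score.

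It would also go too far to call masking the only protection available. The rubric, the standard criteria and the two assessors do limit discretion, and masking would itself be imperfect because post-workshop content may give the time point away.

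Finally, the bias sizes are assumed, the project is described as exploratory with cautious interpretation, and no primary outcome is named. All of this stands and lowers the severity. It does not remove the point.

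**Conclusion.** The point holds in limited form. For an uncontrolled pre-post outcome presented as objective, the stated safeguards deal with disagreement between assessors and leave shared leniency toward post-workshop answers unaddressed. The sentence on kappa also credits it with something it cannot do.

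If leniency occurs, its full amount enters the estimated change. A bias of 0.1 to 0.3 SD of the paired difference would raise the false-positive rate at n = 42 from 5% to about 10% to 48%. This rests on assumed bias sizes, a two-sided 0.05 level and no true effect. Whether any bias will arise, and how large it would be, cannot be known from the article.

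The change is desirable because it is nearly free and is hard to make after unmasked grading, short of regrading everything. It is not a condition for the study to proceed: nothing confirmatory is tied to the rubric P value, and the lack of a control group would limit causal reading even with perfect masking.

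**What to change.** In Data Collection Tools and Content Validity, state that:

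- written answers are held until collection is complete (including the 4-month questionnaire, if the video task is repeated there);
- name, discipline, date and time-point labels are removed, and all answers are pooled in random order;
- both assessors grade the mixed batch independently, with collaboration limited to training and piloting;
- the mean of the two assessors' scores is analysed.

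Reword the kappa sentence so that it claims agreement only. Because both assessors already grade everything, also report agreement on the study answers: weighted kappa for the ordinal domains and an intraclass correlation coefficient for the total. Present this as a secondary check of reliability, not of bias.

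Cost: a REDCap export with a random-order column and a few lines of text, with the same two assessors and no added participants or visits. Downsides: pre-workshop grades are available only after collection ends, and masking remains incomplete where the content of an answer reveals its time point. That limit should be acknowledged when results are reported.
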